## Abstract

**Background:**

Dementia is a global public health priority with an estimated prevalence of 150 million by 2050, nearly two-thirds of whom will live in the Asia-Pacific region. Dementia creates significant care needs for people with the disease, their families, and carers. iSupport is a self-help platform developed by the World Health Organization (WHO) to provide education, skills training, and support to dementia carers. It has been adapted in some contexts (Australia, India, the Netherlands, and Portugal). Carers using the existing adapted versions have identified the need to have a more user-friendly version that enables them to identify solutions for immediate problems quickly in real time. The iSupport virtual assistant (iSupport VA) is being developed to address this gap and will be evaluated in a randomized controlled trial (RCT).

**Objective:**

This paper reports the protocol of a pilot RCT evaluating the iSupport VA.

**Methods:**

Seven versions of iSupport VA will be evaluated in Australia, Indonesia, New Zealand, and Vietnam in a pilot RCT. Feasibility, acceptability, intention to use, and preliminary impact on carer-perceived stress of the iSupport VA intervention will be assessed.

**Results:**

This study was funded by the e-ASIA Joint Research Program in November 2020. From January to July 2023, we will enroll 140 dementia carers (20 carers per iSupport VA version) for the pilot RCT. The study has been approved by the Human Research Committee, University of South Australia, Australia (203455).

**Conclusions:**

This protocol outlines how a technologically enhanced version of the WHO iSupport program—the iSupport VA—will be evaluated. The findings from this intervention study will provide evidence on the feasibility and acceptability of the iSupport VA intervention, which will be the basis for conducting a full RCT to assess the effectiveness of the iSupport VA. The study will be an important reference for countries planning to adapt and enhance the WHO iSupport program using digital health solutions.

**Trial Registration:**

Australian New Zealand Clinical Trials Registry ACTRN12621001452886; https://tinyurl.com/afum5tjz

**International Registered Report Identifier (IRRID):**

PRR1-10.2196/33572

## Introduction

Dementia is a global public health priority, and its global prevalence is growing exponentially [1], tripling from 46.8 million in 2015 to approximately 150 million by 2050 [2]. The fastest growth is occurring in the Asia-Pacific region, where 70 million people are estimated to be living with dementia by 2050 [3]. Dementia is among the leading causes of disability and dependency in older people, creating significant care needs for people with dementia, their families, and carers, affecting social, health, well-being, and economic dimensions [1,2]. In 2018, dementia was estimated to cost US $1 trillion worldwide, and the cost is predicted to rise to US $2 trillion by 2030 [2]. The catastrophic costs of long-term care drive many families of people with dementia into poverty, strain health and social systems, and is a significant impost on government budgets [1].

Approximately 60% of people with dementia live in low- and middle-income countries (LMICs) and the costs of care are mostly borne by family members [2]. Health and social care systems in LMICs are often not well-developed or well-funded, resulting in unmet care needs for people with dementia and their carers [3,4]. In high-income countries (HICs), most people with dementia also live at home and receive care from their families [3,5]. Health and social care systems in HICs are often fragmented and unable to meet all the needs of people with dementia, especially people from culturally and linguistically diverse (CALD) groups [6]. For example, care arrangements and family carer input are disproportionately high for CALD people with dementia in Australia [7] and Māori families in New Zealand [6], which result in them experiencing more psychological and economic burdens associated with care.

Provision of unpaid care often exposes family carers to pronounced stress, resulting in mental and physical health deterioration, and loss of productivity and income [1,3]. Women, who provide the bulk of family care, are disproportionately affected [8]. In LMICs where aged care facilities and other formal support services are underdeveloped, such impacts can be devastating [9]. Supporting family carers through low-cost and sustainable nonpharmacological approaches is much needed to avoid potentially dangerous alternatives with limited efficacy, such as prescribing psychotropic medications, hospitalization, and institutionalization**.** Providing practical support for carers of people with dementia is viewed as an essential part of national dementia plans to maintain the health and well-being of people with dementia, reduce costs related to dementia, and relieve burden on the health and social care systems [10].

Emerging web-based training and support programs have shown positive effects on improving dementia carers’ mental health outcomes with considerable potential for scaling up [11]. To provide practical support for carers, the World Health Organization (WHO) developed “iSupport for Dementia,” a self-learning evidence-based web-based skills training and support program for informal dementia carers, which can be adapted for use in different countries [12]. iSupport offers education, skills training, and support for carers, using problem-solving and cognitive behavioral therapy techniques. The web-based program contains 23 lessons within five modules: (1) what is dementia; (2) being a carer; (3) self-care; (4) providing care; and (5) dealing with behavior changes. Each lesson comprises interactive exercises, and carers receive immediate feedback to their answers, as well as certification when lessons are completed.

The discontinuation of services that has resulted from COVID-19 and its impact on carers of people with dementia (eg, increased social isolation and caregiving burden) emphasizes the need for concise, easy-to-read tips for dementia family carers. This need led the WHO to develop iSupport Lite [13]. Carer feedback from an Australian iSupport adaptation study also demonstrated the need for iSupport enhancement with a more user-friendly version, mechanisms for real-time support, and provision of peer support [14]. They also identified the need to adapt iSupport for CALD communities given their different care needs [14]. iSupport has not been adapted for use in most countries in the Asia-Pacific Region (APR). The exception includes India, where study findings underscored the need to pay close attention to cultural adaptations of the program to improve its acceptability and accessibility [15]. However, cultural adaptation of the iSupport program requires resources, which may not be achievable in many LMICs in the APR. International collaboration is much needed to address the resource issues.

A dearth of scientific evidence on effective cultural adaptation is significant impediments for the uptake of iSupport in many APR countries grappling with the public health challenges of dementia. The e-ASIA funded e-DiVA project addresses these gaps by (1) developing and evaluating an iSupport virtual assistant (VA) to support dementia carers through a partnership among four APR countries: Australia, Indonesia, New Zealand, and Vietnam; and (2) building capacity of researchers and nongovernment organization (NGO) partners to support this development and evaluation. This paper reports the protocol of a pilot randomized control trial (RCT) evaluating the iSupport VA.

## Methods

### Methodological Approaches

This study will operationalize the UK Medical Research Council guidelines for developing and evaluating complex interventions and will focus on the first two stages of this guide: (1) development and (2) feasibility and piloting [16]. A co-design approach will be applied to involve carers in the design process, focusing on the challenges and issues from their perspective and designing solutions to enhance desirability, acceptability, and usability of the intervention [17]. This work will culminate in the development of the iSupport VA comprising a website and a smart device app that will allow carers to search topics of their choice using text or voice commands and provide video instruction to support them in their caring role. Feasibility, acceptability, intention to use, and preliminary impact on carer perceived stress of the iSupport VA will be conducted via a pilot RCT using established approaches [18,19].

### Theoretical Approach

Guided by the Stress/Health model [20], this study proposes to address the identified gaps through a 3-year research program, which uses established theoretical and methodological approaches to culturally and contextually adapt WHO iSupport for use in the aforementioned 4 countries [21]. The Stress/Health model provides a theoretical framework for understanding multidimensional stressors (primary stressors: care recipients’ changed behavior and disability; secondary stressors: family conflict and work difficulty) and adaptive capacities (coping and social support) that collectively affect carer mental health or well-being [22]. iSupport is a multi-component intervention that builds carer skills for managing different stressors and improving adaptive capacities to improve carer mental health and well-being.

### Study Design

A pilot, waitlist RCT will be used with 140 carers (20 carers for each of the 7 versions of iSupport VA (English, Bahasa, and Vietnamese in Australia; Vietnamese in Vietnam; Bahasa in Indonesia; and English and Maori in New Zealand). Carers will be randomized into (1) an intervention group (10 carers per version of iSupport VA) that will use the iSupport VA for 6 months immediately following randomization, or (2) a waiting list control group (10 carers/version) that will receive access to the iSupport VA 3 months after randomization (Figure 1). While pilot studies are not powered to examine effectiveness, this pilot RCT will provide data about acceptability, useability, and preliminary impact of the intervention, as well as the feasibility of the methods and procedures [18] for a fully powered RCT to test effectiveness.

**Figure 1 figure1:**
[figure not shown]
Flow diagram of the pilot randomized controlled trial. PHQ-9: Patient Health Questionnaire, 9-item; VA: virtual assistant.

#### Inclusion Criteria

Participants eligible for the pilot RCT study will (1) be adults (≥18 years) residing in one of the aforementioned 4 countries (2) be a primary unpaid carer of a community-dwelling person with dementia (having a formal diagnosis of dementia as reported by the carer or an Ascertain Dementia 8-item Informant Questionnaires (AD-8) score of ≥2) [23], (3) have been cohabiting and providing care for ≥6 months, and (4) experience stress (a Perceived Stress Scale [PSS] score >13) [24].

#### Exclusion Criteria

Exclusion criteria are (1) inability to comprehend any of the designated languages, (2) having cognitive impairment (Mini-Cog < 4) [25], (3) having significant vision impairment (cannot read what is on the screen to respond appropriately), (4) having hearing impairment (cannot hear the question “What is your name?” on the telephone to respond appropriately), (5) participation in the adaptation and development process of iSupport VA, (6) having no experience in using the internet or apps on devices, and (7) having no access to a device with an internet connection.

#### Recruitment Procedure

Multiple recruitment strategies will be used. Our local NGO partners (eg, Dementia Australia [DA], Alzheimer’s Indonesia [ALZI], and Alzheimers New Zealand) and local clinics and hospitals will announce the study on their website, social media pages, and newsletter. In Australia, study announcements will also be placed in memory and geriatric clinics managed by the Southern Adelaide Local Health Network, and Resthaven South Australia, the Step-Up for Dementia Research group in New South Wales and Western Australia, and the National Ageing Research Institute (NARI)’s CALD Research Engagement Network, the latter hosts a database of >1000 CALD community groups across Australia. We will leave brochures and posters in hospitals, clinics, senior centers that collaborate with ALZI in Indonesia, dementia services at local District Health Boards in New Zealand, and memory clinics and dementia units in hospitals in Vietnam. Treating clinicians of people with dementia will advise carers about the study during their consultations. All study announcements will refer to our e-DiVA project website, where carers interested in the study can register to participate. Potential participants will be contacted by telephone and email or text message via mobile phones and will receive study information and eligibility screening questions, and will be directed to the web-based written informed consent form. Carers who fulfil eligibility criteria and provide consent will receive a weblink to the internet-based battery of baseline questionnaires and will then be included in the study.

### Randomization Procedure

After enrollment, carers will be randomized separately for each iSupport VA version to either intervention or waiting list control groups (1:1 ratio). A permuted block randomization of size 4 will be used to ensure an even balance of carers in each group throughout the study period. A central clinical trials service in Australia will undertake randomization for each iSupport version in the aforementioned 4 countries.

### Interventions

Seven versions of the iSupport VA, comprising a web-based app, will be built from the content of the adapted iSupport. The VA will be designed to make the iSupport program easier and simpler to use on all device types including smart phones, tablets, and laptop and desktop computers. The VA will first ask individual carers in their respective languages to undergo an assessment of their key education and support needs. Using the finding of this initial need assessment, the algorithm of the VA will provide tailored interventions (ie, recommending specific modules or lessons in the iSupport program) to match each individual’s need profiles. The VA will provide text or voice command search options (similar to Google Assistant). The search outcomes will be in text, picture, or video formats with detailed instructions. Users can choose specific modules or any part of the program simply by selecting a specific topic.

Weblinks for existing health and well-being, aged, and social care services for dementia and other important information (eg, first-aid tips, emergency contact numbers, etc) in each country will be incorporated in VA versions. With carers’ consent, the VA will support web-based peer support groups. These peer support groups will enable sharing of experiences, practical tips, and peer support either in real time video or through text chats among logged in members, or through an asynchronous messaging system. The app will have the capability for a “Personal Diary” for users to write their action plans or scheduled medical appointments and will remind users to follow the scheduled plans and appointments.

Carers randomized to the intervention group will receive a weblink to the iSupport VA app together with the intervention login details, and they will have access to the intervention for 6 months immediately after randomization. Those in the waiting list control group will also receive the iSupport VA. However, they will be informed that they will receive login details for iSupport VA after completing the 3-month assessment. After completing their 3-month assessment, all waiting list control carers will have full access to iSupport VA for 3 months, which will increase the number of dementia carers to access the iSupport VA in this pilot RCT. Intervention dose will be defined as the percentage of lessons completed of the total lessons recommended by the iSupport VA at 3 months in the intervention group, based on the initial need assessment. Monthly phone contact with carers will be also conducted to assess their use of the intervention. Notes from these contacts will be recorded. A local research team member fluent in the country’s appropriate language will be available and contactable by telephone or email if carers need technical assistance.

### Outcomes

The intervention feasibility will be evaluated with reference to recruitment, randomization, retention, treatment adherence, and assessment processes [18]. At the end of the RCT, carers in the intervention group (10 per iSupport VA version) will undergo a 30-60–minute semi-structured exit interview to assess iSupport VA acceptability, including most and least relevant and helpful aspects, the main barriers and facilitators of using the VA, and recommended improvements. All 140 carers will be asked to complete a questionnaire to assess their intention to use the iSupport VA. The questionnaire will include one question: “How will you (dementia carer) use the iSupport VA in the coming six months?” Guided by the Unified Theory of Acceptance and Use of Technology (UTAUT) [19], the questionnaire will assess the direct determinants of intention. These are performance expectancy (the degree to which using the iSupport VA will provide benefits in performing caring role), effort expectancy (the degree of ease associated with the use of the VA), and social influence (the degree to which a carer perceives that others vital to them believe that they should use the VA).

Outcomes will be assessed within the iSupport web-based tool using encryption for data protection at baseline (t_0_), post-intervention (3 months after baseline; t_1_), and follow-up (6 months after baseline; t_2_). For measuring the preliminary impact, the primary outcome will be change in perceived stress [24] at t_1_. The secondary outcomes will include change in psychological distress [26] and global Visual Analogue Scale quality of life [27] at t_1_. To account for a potential contamination of the control group owing to the availability of the generic version of WHO iSupport web-based program, at their 3-month assessment, carers in the control group will be asked if they have accessed the WHO iSupport manual or generic web-based program. Where local-language versions are unavailable, study instruments will be translated and back-translated, followed by reconciliation and review by bilingual experts to develop local language versions. The baseline measures will include language version, characteristics of carers (age; sex; ethnicity; educational, occupational and economic attainments; cohabitation status; and relationship with the care recipient), and care recipients (age, sex, dementia duration, type, and severity [28], and behavioral and psychological symptoms [29]). Further analysis will include a comparison of change in outcomes in the 2 groups between t_0_ and t_3_. This will compare long-term use (6 months) of the tool versus short-term (3 months).

### Analyses and Evaluation

Recruitment feasibility will be assessed on the basis of the number of carers screened to identify carers who meet eligibility criteria. Randomization feasibility will be assessed on the basis of the percentage of eligible carers who agree to randomization. Subject retention in both arms of the study will be evaluated. We will also track intervention adherence (eg, the rate of completing lessons recommended by the VA based on the initial carer need assessment). We will assess the feasibility of assessing study outcomes in terms of the percentage of the baseline, 3-, and 6-month assessments completed and the completeness of the collected data. The criteria for determining feasibility success will be as follows: (1) average of 3 carers per iSupport version per month (approximately 140 carers for 7 iSupport VA versions in the aforementioned 4 countries over 7 months) can be recruited; (2) at least 70% of all eligible carers can be recruited; (3) complete baseline and follow-up assessments by at least 70% of all recruited carers. iSupport VA acceptability will be analyzed thematically. The association between the UTAUT construct [19] and the intention to use iSupport VA will be assessed using logistic regression analyses. For preliminary impact assessment, linear mixed-effects modeling will be used to analyze changes in primary and secondary outcomes from baseline to 3 and 6 months. For dichotomous or noncontiguous outcome measures, appropriate generalized linear mixed-effects models will be applied. All analyses will be adjusted for the language version. One chief investigator of the project is a biostatistician, who will support the research and RCT from designing, collecting, analyzing, and presenting the data. A detailed statistical analysis plan will be developed before unbinding the data and any analyses.

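### The regression of intention to use on the UTAUT constructs should include randomised arm, because the arms differ in length of VA access at any common assessment

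*Protocol article*

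**What the plan says.** **Respondents.** The Outcomes section says: "All 140 carers will be asked to complete a questionnaire to assess their intention to use the iSupport VA". The questionnaire has one question on use of the VA over the next six months. It also measures performance expectancy, effort expectancy and social influence, which the section presents as the direct determinants of intention.

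**Model.** Analyses and Evaluation says: "The association between the UTAUT construct [19] and the intention to use iSupport VA will be assessed using logistic regression analyses". Later in the same section comes the general rule: "All analyses will be adjusted for the language version". No other covariate is named for this model. The section announces a detailed statistical analysis plan, which is not shown.

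**Access.** Under Interventions, intervention carers get a login and "they will have access to the intervention for 6 months immediately after randomization". After their 3-month assessment, "all waiting list control carers will have full access to iSupport VA for 3 months".

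**Timing.** The article does not say when the intention questionnaire is given. The nearest time reference belongs to the interview of one arm: "At the end of the RCT, carers in the intervention group (10 per iSupport VA version) will undergo a 30-60–minute semi-structured exit interview".

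**The concern.** Perceived ease and perceived benefit are plausibly shaped by use, so carers with longer access may score differently on the constructs. Length of access may also change intention directly. For example, the lessons recommended to a carer are a finite set. A carer who has had longer to complete them may plan less further use, even while rating the VA easy and helpful. If both happen, arm is a common cause of predictor and outcome. A model without arm then attributes part of the arm difference to the constructs, which can suggest a determinant that is not there or weaken one that is.

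Intention to use is one of the four assessment aims in the Abstract and under Methodological Approaches. The Outcomes section itself treats 6 versus 3 months of use as a contrast worth analysing for the other outcomes.

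**Working it through.** **1. Sample and balance.** 7 versions × 20 carers = 140, which reproduces the stated total and gives 70 per arm. Each version's 20 carers fill 20 / 4 = 5 complete blocks of size 4, so arm is 10:10 within version. Arm and version are therefore uncorrelated by design, and a version term removes none of an arm difference.

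**2. Access at each possible time of asking.**

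| When asked | Intervention | Waiting list |
|---|---|---|
| Both arms at month 3 | 3 months | 0 months |
| Both arms at month 6 | 6 months | 3 months |
| Each arm after 3 months of use (months 3 and 6) | 3 months | 3 months |

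Only the last schedule equalises access, and nothing in the article describes it.

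**3. When omitting arm biases the odds ratio.** Let arm shift a construct by *d* within-arm SDs, and shift the log-odds of intention by *g* through a path outside the construct. With 1:1 allocation and within-arm SD 1, the covariance of construct and arm is d/4 and the construct's variance is 1 + d²/4. To a first approximation:

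bias in log OR ≈ g × (d/4) / (1 + d²/4)

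This is zero if either *d* or *g* is zero. For d = 0.5 and g = 0.7: 0.7 × 0.125 / 1.0625 = 0.082, so the OR is 1.09 when the truth is 1.00.

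**4. Size under assumed shifts.** The documents give no values for *d*, *g* or the proportion intending to use, so all are assumptions. Every trial has n = 140, one construct, no true association and a two-sided 5% test. Set A has 50% intention and no version term (OR from n = 400,000, error rates from 3,000 trials). Set B has 70% intention and version terms (1,500 trials, median OR).

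| Set | d | g | Implied intention by arm | OR by formula | OR simulated, no arm term | False positives, no arm term | With arm term |
|---|---|---|---|---|---|---|---|
| A | 0.2 | 0.3 | 46% v 54% | 1.01 | 1.01 | 5.6% | 5.8% |
| A | 0.5 | 0.7 | 41% v 59% | 1.09 | 1.09 | 7.3% | 4.4% |
| B | 0.5 | 1.0 | 59% v 79% | 1.12 | 1.14 | 10.7% | 5.1% |
| B | 0.5 | −1.0 | 79% v 59% | 0.89 | 0.88 | 9.9% | 4.6% |
| A | 0.8 | 1.1 | 37% v 63% | 1.21 | 1.21 | 21.8% | 4.7% |
| B | 0.8 | 1.5 | 52% v 83% | 1.30 | 1.31 | 31.8% | 5.7% |
| B | 0.8 | −1.5 | 83% v 52% | 0.77 | 0.76 | 31.7% | 5.7% |

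The standard error of the log OR at n = 140 is about 0.20. The bias of 0.08 in the second row is therefore about 0.4 standard errors.

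**5. With a true association.** In set A, with a true OR of 2.01, the model without arm gives 2.05, 2.14 and 2.35 for its three rows; with arm it gives 2.01 to 2.02. In set B, with a true OR of 2.0, d = 0.8 and g = −1.5, the model without arm gives 1.49 with power 58%; with arm it gives 2.10 with power 93%.

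**6. When there is nothing to correct.** With g = 0 the model without arm is unbiased: OR 0.99 to 1.00 for a truth of 1.0, and 2.00 to 2.03 for a truth of 2.01. With d = 0 there is no confounding. The OR then falls only from 2.01 to 1.92 at g = 1.1, which is non-collapsibility. With neither shift, adding arm changes power from 95.5% to 95.2%.

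**The case against.** The strongest reply is that this is silence in a condensed article and not a wrong choice. Four parts of it stand.

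- **The covariate list is not closed.** A reader might infer that the model adjusts for language version and nothing else. The sentence sets an adjustment common to all analyses. Read as exhaustive, it would also bar arm from the mixed models for perceived stress, which cannot be meant. The announced analysis plan may add arm.
- **Timing is not fixed.** A reader might infer that the arms certainly answer after different lengths of access. That follows only if both are asked at the same assessment, which is likely but not stated.
- **Confounding is not shown.** A reader might infer that the construct odds ratios are confounded. The documents do not establish this. The article calls the constructs direct determinants, and if access acts on intention only through them, omitting arm causes no bias. A direct path is plausible but conjectural, and the large scenarios need arm differences in intention of roughly 26 to 31 percentage points outside the constructs.
- **No pooled intention figure is planned.** A reader might object to a single intention proportion across two lengths of use. The article specifies an association, and none of its three feasibility criteria uses intention.

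What the reply does not remove is that a model with arm is at least as good in every scenario examined, apart from differences within simulation error. Arm is randomised and precedes both constructs and intention, so conditioning on it introduces no bias of its own.

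**Conclusion.** The point holds as a low-cost improvement to an exploratory pilot analysis, and not as an error. The article brings both arms into the intention questionnaire, names a logistic model and names one adjustment, which is balanced against arm and so cannot stand in for it. Any confounding by arm is conditional: access must differ when carers answer, must shift a construct, and must shift intention outside the constructs. Under small or moderate assumed shifts the effect is negligible to modest, with false-positive rates of about 5.6% to 10%. It is substantial, at about 22% to 32%, only under large shifts, and absent if arm acts only through the constructs. These sizes rest on assumed shifts and a single construct, whereas the questionnaire has three. No stated figure is wrong and no two passages conflict.

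**What to change.** In Analyses and Evaluation, or in the announced statistical analysis plan, state that the regression of intention on the UTAUT constructs includes randomised arm as a covariate next to language version. State also that intention and each construct are reported by arm, with the arm difference and its 95% confidence interval. It would help to say at which assessment each arm receives the questionnaire.

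The cost is one extra parameter in a small logistic model, and wider intervals for by-arm summaries (70 carers each) than for all 140. No new data, visits or carers are needed.

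### The impact model does not say how the baseline stress score enters; read as a plain change-score analysis it would give up some precision, and its adjustment term should name the seven randomisation strata (minor)

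*Protocol article*

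**What the plan says.** The Outcomes section of the protocol article fixes the primary impact outcome: "the primary outcome will be change in perceived stress [24] at t_1", where t1 is 3 months after baseline. Under Analyses and Evaluation, "linear mixed-effects modeling will be used to analyze changes in primary and secondary outcomes from baseline to 3 and 6 months", followed by "All analyses will be adjusted for the language version". No other covariate is named. The same section defers detail to a statistical analysis plan, to be written before the data are unblinded.

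On allocation, the Randomization Procedure says "carers will be randomized separately for each iSupport VA version to either intervention or waiting list control groups (1:1 ratio"), and "A permuted block randomization of size 4 will be used". Study Design lists the seven versions as "English, Bahasa, and Vietnamese in Australia; Vietnamese in Vietnam; Bahasa in Indonesia; and English and Maori in New Zealand". Those are seven language-by-country combinations in four languages; English, Bahasa and Vietnamese each occur in two countries. Language version reappears in Outcomes as a baseline measure, without a definition.

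**The concern.** Two things are left open by wording that is otherwise quite specific.

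First, the outcome is defined as change, and the baseline score is not made part of the model. An analyst could follow the text faithfully by modelling change scores, or by fitting the repeated measures with a separate baseline mean in each arm. Both give the simple difference in mean change at 3 months. Under randomisation that is unbiased, but it is less efficient than an analysis that uses the baseline score. The pilot is meant to be the basis for a full trial, so its effect estimate should be as precise as the data already collected permit.

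Second, the adjustment is stated for all analyses in a term that differs from the randomisation unit. If it were read as language, Australian strata would be merged with those in Vietnam, Indonesia and New Zealand.

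**Working it through.** **Sample size.** 7 versions × 20 carers = 140, or 70 per arm. Twenty per version is five complete blocks of 4, so 10:10 within each version. The article gives no standard deviation, correlation or power calculation, so everything below rests on assumed values.

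**1. Cost of omitting the baseline score, no truncation.** Let s² be the common variance at baseline and follow-up, and r their correlation.

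- Variance of a change score: 2(1 − r)s²
- Residual variance after baseline adjustment: (1 − r²)s²
- Ratio: (1 + r)/2

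| Assumed r | Ratio | Variance reduction | Standard error reduction | 95% half-width, change → adjusted (in s, 70 per arm) |
|---|---|---|---|---|
| 0.3 | 0.65 | 35% | 19.4% | 0.392 → 0.316 |
| 0.5 | 0.75 | 25% | 13.4% | 0.331 → 0.287 |
| 0.7 | 0.85 | 15% | 7.8% | 0.257 → 0.237 |

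The half-width is 1.96 × √(variance × 2/70). With an assumed standard deviation of 6 points and r = 0.5 it is 1.96 × 6 × √(2/70) = 1.99 points for change and 1.96 × 6 × √(0.75 × 2/70) = 1.72 points with adjustment.

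**2. Does a mixed model avoid the loss?** Generalised least squares for baseline and 3 months, 70 per arm, r = 0.5:

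- Free baseline mean per arm: variance of the 3-month effect 0.0286 s², the same as for change scores (2 × 1.0/70).
- Baseline mean constrained equal across arms: 0.0214 s², the same as baseline as covariate (2 × 0.75/70).

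So the loss depends entirely on a choice that the article does not state.

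**3. Effect of the entry threshold (stress score above 13).** Selecting on the baseline score leaves the regression slope and the residual variance unchanged and shrinks only the baseline variance. Then

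variance of change = residual variance + (1 − slope)² × baseline variance.

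Take the untruncated variance as 1, the slope as r, and a truncated baseline variance of 0.5 (assumed):

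- r = 0.3: 0.91 + 0.5 × 0.49 = 1.155; 0.91/1.155 = 0.788, reduction 21%
- r = 0.5: 0.75 + 0.5 × 0.25 = 0.875; 0.75/0.875 = 0.857, reduction 14%
- r = 0.7: 0.51 + 0.5 × 0.09 = 0.555; 0.51/0.555 = 0.919, reduction 8%

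With the cut at the mean of a normal distribution, the baseline variance is 1 − 2/π = 0.363. At r = 0.5 the ratio is 0.75/(0.75 + 0.25 × 0.363) = 0.892, a reduction of 11%.

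This assumes that the score deciding entry is also the baseline score. The Recruitment Procedure places screening questions before the baseline battery, so they may be separate measurements. With a cut at the screening mean and r = 0.5 between each of screening and baseline and follow-up, the ratio is 0.83 if screening and baseline correlate 0.9 (reduction 17%) and 0.70 if they correlate only 0.5 (reduction 30%).

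**4. Four languages or seven versions.** Simulation of 140 carers, 10:10 in each of seven strata, residual standard deviation 1, no treatment effect, 2,000 runs per setting:

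| Between-version SD | Standard error, 4 languages | Standard error, 7 versions | Type I error, 4 / 7 |
|---|---|---|---|
| 0.2 | 0.1699 | 0.1685 | 5.1% / 5.3% |
| 0.4 | 0.1742 | 0.1683 | 4.2% / 5.0% |
| 0.6 | 0.1811 | 0.1686 | 4.2% / 5.3% |

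The point estimate was the same under both adjustments in every run, to rounding error. The four-language standard error is larger by about 1%, 4% and 7%. The simulation error of a 5% rate is √(0.05 × 0.95/2000) = 0.5 percentage points, so the type I error figures show at most mild conservatism.

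**The case against.** The strongest reply is that the article promises a detailed analysis plan, and that the way baseline enters a mixed model is ordinary content for it. That stands as a limit on the point: nothing here is missing from the protocol. What remains is that the article does fix the outcome as change and does name an adjustment, and an analysis faithful to both could be the less efficient one.

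A reader might infer more than the text supports, in four ways.

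- *That adjustment is restricted to language version.* The article names that factor and excludes no other.
- *That precision is certainly lost.* A mixed model of changes from baseline can equally be a repeated-measures model with a common baseline mean, which loses nothing.
- *That the entry threshold enlarges the loss by lowering the correlation.* Putting a truncated correlation into (1 + r)/2 is invalid, because that formula needs equal variances, and direct selection on baseline breaks this. The loss then gets smaller. Only selection on a separate and weakly correlated screening score could reverse this, and the article does not establish that.
- *That the analysis departs from the randomisation.* The article uses the word version for the seven language-by-country builds, so seven is a natural reading. Even the four-language reading gives no bias with complete, balanced data.

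It is also fair that the pilot is expressly not powered for effectiveness and that its success criteria concern feasibility. No stated decision turns on a half-width of 1.99 rather than 1.72 points.

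**Conclusion.** The point holds as a minor, conditional improvement. If the 3-month arm difference is estimated from change scores, or with free baseline means per arm, its variance is higher than it need be. Baseline adjustment would cut it by 35%, 25% or 15% at assumed correlations of 0.3, 0.5 and 0.7 without truncation, and by about 21%, 14% or 8% if the entry threshold acts on the baseline score and halves its variance. If a common baseline mean is already intended, the loss is zero. The adjustment term should be defined; on the adverse reading the cost is a standard error too large by roughly 1% to 7% over the between-version spreads tried, with no change to the complete-data estimate. None of this invalidates the pilot.

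**What to change.** State in the analysis plan, and in any protocol update, that the arm difference in perceived stress at 3 months, with its 95% confidence interval, comes from a linear mixed model with categorical time and arm-by-time terms. The baseline score should enter either as a covariate, with the 3- and 6-month scores as outcomes, or as an outcome whose mean is constrained equal across arms. Replace language version by the seven iSupport VA versions used as randomisation strata, entered as a fixed effect.

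The cost is two sentences. The baseline score and the version are already collected, and the Trial Status section says that enrolment has not begun.
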